## Abstract

**Background:**

Many people with intellectual disability present with challenging behaviour which often has serious consequences such as the prescription of long term medication, in-patient admissions and disruption of normal daily activities. Small scale studies of Positive Behaviour Support (PBS) delivered by paid carers suggest that it reduces challenging behaviour and costs of care and improves quality of life. This study aims to investigate whether professionals training in the delivery of PBS as part of routine practice is clinically and cost effective compared to treatment as usual in community intellectual disability services.

**Method:**

The study is a multi-centre cluster randomised controlled trial involving community intellectual disability services in England and service users with mild to severe intellectual disability and challenging behaviour. The teams will be randomly allocated into one of two conditions, either training and support to deliver PBS or treatment as usual. We will carry out assessments of challenging behaviour, use of services, quality of life, mental health, and family and paid carer burden at six and 12 months. We will monitor treatment fidelity and we will interview a sample of paid and family carers, service users, staff and managers about what they think of the treatment and how best we can deliver it in routine care. The main outcome is reduction in challenging behaviour at one year after randomisation. We will also carry out a health economic evaluation to examine the costs and consequences of staff training in PBS.

**Discussion:**

The study findings will have significant implications for the delivery of PBS in community based services with the potential for reducing inpatient admissions and out-of-area placements for adults with intellectual disability and challenging behaviour.

**Trial registration:**

This trial is registered with Clinical Trials.gov (Ref NCT01680276).

Clinical Trials Unit: PRIMENT https://www.ucl.ac.uk/priment/.

**Electronic supplementary material:**

The online version of this article (doi:10.1186/s12888-014-0219-6) contains supplementary material, which is available to authorized users.

## Background

Intellectual disability is a disorder that includes impairments in three domains, i.e. cognitive ability, social skills and adaptive abilities and it should be evident during development [1]. There are estimated to be 800,000 people with mild and 112,000 people with severe intellectual disability in the UK [2]. Challenging behaviours are common in this population with a point prevalence in adults of 22.5% and a two year incidence of 4.6% [3]. Aggression is by far the commonest type of challenging behaviour with a reported prevalence of 11% to 27% [4]. Challenging behaviour is associated with increase in receipt of antipsychotic medication, service use, hospitalisation, restrictive care practices and deprivation [5-8]

Reduction of challenging behaviour has been the focus of many interventional approaches over the years. Most of the literature comprises small-n and single case empirical research delivering a variety of pharmacological and psychosocial treatments [9-12]. However, there are few well conducted RCTs and the findings of those that have been carried out are inconclusive; most notably, a trial of antipsychotics showed that they were no more effective than placebo [13] in reducing challenging behaviour. Overall, existing RCTs are small, subject to bias, have only examined short-term outcomes and lack a cost effectiveness component or reports on health related quality of life. A pilot RCT (n = 63) showed that Applied Behaviour Analysis (ABA) delivered by a specialist team can significantly improve irritability, lethargy and hyperactivity and may be cost neutral over six months [11]. Furthermore, a naturalistic follow-up for two years after randomisation showed a sustained positive effect of the intervention on challenging behaviour [12]. An additional qualitative exploration of the opinions of those involved in the trial (patients, carers and staff) revealed that there was strong support for clinical trials as a method of evaluating psychological therapies to treat challenging behaviour [14].

### The financial burden of challenging behaviour

European data on the cost of disorders of the brain [15] estimate that the cost of intellectual disabilities is 43bn euros most of which is accounted for by costs of direct health and non-medical care. A survey of five London areas showed that 67% (£14 million, 2004–2005 prices) of combined medical and social care budgets supported 134 out-of-area placements for adults with intellectual disability and challenging behaviour [16]. Individual care packages commonly ranged from £100 k to 450 k per annum. Other studies indicate that costs are higher for people with more severe intellectual disability and those with greater levels of challenging behaviour, with specialist accommodation accounting for the majority of the cost [17-19].

### The origins of PBS

Positive Behaviour Support (PBS) and its precursor ABA are multicomponent methods that purport to support people with intellectual disability and challenging behaviour [20,21]. PBS more specifically has developed into a discipline that focuses on the influence of the environment on behaviour rather than solely on the internal drivers of the behaviours [22]. PBS based practice consists of a flexible, multicomponent intervention which takes a lifespan perspective, emphasises prevention and fosters stakeholder participation. PBS practice includes a functional assessment of the possible relationships between specific environmental events and the target behaviours. By identifying what reinforces the behaviour, practitioners can put in place interventions which are designed to foster prosocial actions. The final aim is to enhance the person’s quality of life and his/her integration within the local community. An important tenet of PBS is that challenging behaviour is shaped by personal and psychological experiences and helps the person, with often severe intellectual disability, to exert some control over his/her environment. The challenging behaviour may be a response to environmental cues or “schedule-induced”, that is, present as a result of interactions between the individual and the environment. These concepts have influenced the definition of challenging behaviour as “*behaviour of such intensity, frequency or duration that the physical safety of the person or others is placed in serious jeopardy or behaviour which is likely to seriously limit or deny access to the use of ordinary community facilities*” [23].

PBS is a widely applied complex intervention to a number of conditions such as autism spectrum disorders, in education, mental health and other fields in health and social care.

### PBS based staff training

Specific staff competencies are a crucial factor in maintaining improvements in behaviour. However, given the resource associated with delivering PBS, only about half of service users in need of PBS may be treated at any time [24]. Lack of competencies in managing challenging behaviour is also an important factor in perpetuating out-of-area placements [25,26]. Even where there are tertiary specialist teams which provide ABA/PBS, service users often have to wait several months to receive help.

One approach to meeting this shortfall is to train paid carers and professional staff in PBS. McClean et al. [24] and Grey & McClean [27] have reported descriptive data on training 132 paid carers in a non randomised clinical study (n = 60) that reported significant reductions in challenging behaviour in people in the target group compared with controls. However, the instrument used to measure the primary outcome does not have established psychometric properties, the study was uncontrolled and included training paid carers (rather than professionals), who are likely to require a different set of skills and knowledge from the outset. The authors estimated that PBS based training may lead to savings of £2 K per person treated.

The central objective of good practice in treating challenging behaviour is maintain individuals who present with such behaviours locally and to avoid transfers to out-of-area facilities [28]. Other guidance advocates a person centred approach encompassing tenets of PBS which leads to environments capable to deal with such behaviour and the implementation of skilled commissioning for care provision [29].

We argue that a rigorous evaluation of the clinical and cost effectiveness of PBS delivered by appropriately trained staff is long overdue. The focus of this project is highly relevant given the widespread implementation of PBS and thus the findings would have significant practice and policy benefits internationally. Moreover, the economic analysis will determine whether the intervention incurs costs beyond and above treatment as usual and any reductions in challenging behaviour are associated with reduced use or resources and improved quality of life.

#### Primary objective

To compare changes in carer reported ratings of challenging behaviour at 12 months in adults with intellectual disability who are treated in teams trained to deliver PBS in addition to TAU with those treated in teams that deliver TAU alone.

#### Secondary objectives

i.To compare the costs of care in each arm.ii.To examine the impact of the intervention and TAU at 12 months on prescription of psychotropic medication, burden on family and paid carers, service user mental status, and participation in community-based activities compared to TAU alone.iii.To carry out an exploratory analysis of the impact of the intervention and TAU alone at 12 months on all measures in a sub-sample of participants with autism spectrum disorders (ASD).iv.To measure the influence on the primary outcome of level of intellectual disability, mental status and ASD status and adaptive behaviour scores.

## Methods

### Trial design

Multicentre cluster researcher-masked randomised controlled trial of manualised PBS-based staff training programme for managing challenging behaviour in adults with intellectual disability. The control group will receive treatment as usual. Treatment as usual will also be available to the participants in the intervention arm. The unit of randomisation will be the community intellectual disability service. A cluster randomised design is considered appropriate in the light of this being an educational intervention aimed at groups of professionals and the service [30].

### Sample size

The primary outcome is the total Aberrant Behaviour Checklist (ABC) score measured repeatedly at six and 12 months following recruitment. The pilot study [15] generated mean baseline ABC scores of 45.4 (SD 26.4). A reduction of 0.45 of a standard deviation on the ABC score in the ABC group compared to the TAU group is considered to be clinically important. Using an analysis of covariance approach based on a correlation of 0.48 between the baseline and post-intervention ABC measurements (as per pilot study, 15) 80 patients per arm will be required to detect a difference of 0.45 SD with 90% power and 5% significance level. Inflating for clustering within the community intellectual disability services, using the formula proposed by Eldridge et al. [31] which accounts for variable cluster sizes and an intracluster correlation of 0.062 (estimated from the pilot study), an average cluster size of 12 (we expect it to be 13, however, allowing for 10% attrition and rounding it up to the nearest integer we have used a cluster size of 12 in our calculations), and a standard deviation for the cluster size of 3, a total of 276 patients will be required. However, this sample size can be reduced as each patient will provide two measurements of ABC score. Using a correlation of 0.6 between the 6 and 12 months post intervention ABC measurements (15,16) and a cluster size of 2, a total of 442 ABC measurements from 221 patients will be required. In performing this calculation we have assumed that there will be no treatment by time period interaction over 12 months supported by the pilot studies [11,12]. To allow for 10% attrition over the 12 month period a total of 246 patients will be recruited to the trial thus requiring 19 clusters. The sample size calculation is based on the program and formulae in STATA version 12.

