### Statistical analysis

We shall follow CONSORT guidelines for the analysis of cluster randomised trials and reporting of findings (http://www.consort-statement.org/).

The baseline characteristics of the PBS and TAU groups will be summarised using means, standard deviation and proportions as appropriate. A three level regression model adjusting for baseline ABC measurements, time period and effects of clustering by services and accounting for repeated measures within subjects will be used for the primary analysis. Similar analyses will be conducted for the secondary outcomes using appropriate regression models depending on the type of outcome. Results from all secondary analyses will be presented as estimates with confidence intervals and treated as exploratory. If we encounter missing data, bias due to missing data will be investigated initially by comparing the characteristics of the trial participants with complete follow-up measurements and those who have incomplete follow-up or no outcome data, descriptively. If differences are observed in the participants’ characteristics in the descriptive analysis, factors which are likely to be associated with the outcome will be included in a multilevel logistic regression analysis (with missing yes or no as outcome) to identify predictors of missing data. If predictors associated with both missing data and the outcomes are found, these will be included in the multilevel models examining the effects of intervention on the outcomes [45]. A sensitivity analysis will also be carried out to examine the effect of PBS on ABC score after adjusting for area deprivation and the service staff to patient ratio if appropriate. Multiple imputation may be used as part of the sensitivity analysis accounting for the clustered nature of the data if considered appropriate [46-48]. As part of the sensitivity analysis we will also examine intervention by time period interaction. All analyses will be carried out on an intention to treat basis. A detailed statistical analysis plan will be agreed by the Trial Steering Committee prior to the analysis of unblinded data.

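### The sample size lets the gain from two visits shrink the between-team variance and ignores that only 19 teams are randomised: the stated 90% power is about 83%

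*Protocol article*

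**What the plan says.** The protocol article's Sample size section targets a standardised difference of 0.45. It states that "80 patients per arm will be required" to "detect a difference of 0.45 SD with 90% power and 5% significance level", using analysis of covariance with "a correlation of 0.48 between the baseline and post-intervention ABC measurements". It inflates for clustering with a published formula for unequal clusters (intracluster correlation 0.062, mean cluster size 12, SD of cluster size 3) and reaches 276 patients.

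It then lowers that total because each patient is measured twice: "Using a correlation of 0.6 between the 6 and 12 months post intervention ABC measurements (15,16) and a cluster size of 2" gives 442 measurements from 221 patients. After allowing for 10% attrition, "a total of 246 patients will be recruited to the trial thus requiring 19 clusters".

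Under Trial design, the community service is the unit of randomisation. Under Statistical analysis, the primary model is a three-level regression that adjusts for baseline ABC and time period, with "effects of clustering by services and accounting for repeated measures within subjects".

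**The concern.** There are two separate problems.

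- **Order of the two adjustments.** The reduction for repeated measures is applied to a number that already contains the cluster inflation, so it shrinks both the within-team and the between-team parts of the variance. A second visit to the same patient averages out visit-to-visit noise. It does not average out a service effect that is the same at both visits. That effect falls only with more teams.
- **Number of teams.** The figures follow from normal quantiles. With 19 randomised teams, the treatment contrast has about 19 − 2 = 17 degrees of freedom, which costs further power.

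Both act in the same direction. If the trial finds no effect, readers will take it as the result of a trial with 90% power, when the design as planned has less.

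**Working it through.** **Inputs** (Sample size section unless noted): difference 0.45 SD; power 90%; alpha 5%, taken as two-sided because that reproduces the figures; baseline to follow-up correlation 0.48; intracluster correlation 0.062; mean cluster size 12 with SD 3, so CV = 3/12 = 0.25; correlation between visits 0.6; two visits; attrition 10%; 19 teams. The three-level model comes from the Statistical analysis section.

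**1. The plan's own chain**

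- Per arm: 2 × (1.96 + 1.2816)² × (1 − 0.48²) / 0.45² = 79.9, so 80. Total before clustering: 159.7.
- Cluster design effect: (1 + 0.25²) × 12 = 12.75; 1 + (12.75 − 1) × 0.062 = 1.7285. 159.7 × 1.7285 = 276.
- Two visits: 276 × 1.6 = 442 measurements; 442 / 2 = 221 patients.
- Attrition: 221 / 0.9 = 246. Teams: 246 / 13 = 18.9, so 19.
- Combined variance factor: 0.8 × 1.7285 = 1.3828. Normal power at 221 is 90.0%.

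Every stated figure reproduces. This confirms that the two factors were multiplied and that normal quantiles were used.

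**2. Variance factor under the three-level model**

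For the mean of two visits, with one service effect common to both and relative to the variance of one measurement:

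- visit-level part: (1 − 0.6) / 2 = 0.200
- patient-level part: 0.6 − 0.062 = 0.538
- service-level part, multiplied by the effective cluster size: 0.062 × 12.75 = 0.7905
- sum: 1.5285

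Per measurement this is 1 + 0.6 + 2 × 11.75 × 0.062 = 3.057, against the plan's 1.6 × 1.7285 = 2.766. The product is exact only if service effects at 6 and 12 months correlate at 0.6, which the protocol does not state.

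**3. Power at 221 analysed patients**

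- Needed for 90% on the normal scale: 159.7 × 1.5285 = 244 to 245 analysed. Recruited: 244.2 / 0.9 = 271.3, so about 272; 272 / 13 = 20.9, so 21 teams.
- Noncentrality: 3.2415 × √(221 / 244.2) = 3.084.
- Normal power: 87.0%. Noncentral t on 17 df: 82.8%.
- Simulation with 19 unequal teams: about 84%.
- To reach 90% with t: 23 teams of 12 analysed (276 patients) give 90.7%.

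**4. Each correction alone, and variants**

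| Setting (221 analysed unless noted) | Normal | t, 17 df |
|---|---|---|
| Plan's multiplied factor, 1.3828 | 90.0% | 86.3% |
| Three-level factor, 1.5285 | 87.0% | 82.8% |
| Three-level factor, 228 analysed (19 × 12) | 87.9% | 83.9% |
| 0.6 read as raw: (0.6 − 0.2304) / 0.7696 = 0.48, factor 1.4685 | 88.2% | 84.2% |
| Service effects correlating 0.9 between visits (assumed) | 87.7% | 83.7% |
| Service effects correlating 0.8 between visits (assumed) | 88.5% | 84.6% |
| 12-month visit alone, factor 1.7285 | 82.6% | 78.0% |

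If 0.062 is a raw intracluster correlation and baseline explains none of the service variance, it becomes 0.062 / 0.7696 = 0.081 after adjustment. Power with t is then 78% (visit correlation 0.6) or 79% (0.48).

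**The case against.** The strongest objections are these.

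- **The arithmetic is right, and the multiplication alone costs only about 3 points.** This is true. The error lies in the method of combining the factors, and moving from 90.0% to 87.0% is its whole effect on the plan's normal basis. The remaining 4 points or so come from the t reference. One may say that the choice of degrees of freedom belongs in the analysis plan. For the test itself that is fair. But the power is a printed claim about a design with 19 randomised units, and even with the plan's own factor it is 86.3% on 17 df.
- **The 0.6 reads most naturally as a raw correlation.** It may be. Power with t is then 84.2%, or 85.3% with 228 analysed, which is still short of 90%.
- **The covariance structure of the model is not spelled out.** Correct. A single service intercept is the usual form of a three-level model but is an inference here. Assumed service correlations of 0.8 to 0.9 between visits give 84% to 86% with t across visit correlations of 0.6 and 0.48. Combining the product formula with 0.48 gives 88.8%.
- **Baseline adjustment may lower the intracluster correlation.** This is the best point. If 0.062 is raw and team means correlate 0.7 between baseline and follow-up (an assumption), the adjusted value is 0.062 × (1 − 0.49) / 0.7696 = 0.041. Power with t is then 88.7% (visit correlation 0.6) or 90.1% (0.48). At a team-level correlation of 0.8 it is 92% to 93%. The protocol does not say whether 0.062 is raw or adjusted, so this uncertainty runs both ways and is as large as the error. It does not rescue the stated calculation, which uses 0.062 as it stands.

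**Conclusion.** The concern holds. At the protocol's own inputs, 221 analysed patients in 19 teams give about 83% power for the effect averaged over the two visits, not 90%. The miss rate is about 17%, roughly 1.7 times the stated 10%. About 3 points of the loss come from shrinking the service variance by averaging visits and about 4 from ignoring the small number of teams.

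The figure assumes one service effect shared by both visits, an intracluster correlation of 0.062 and a visit correlation of 0.6 that both apply after baseline adjustment, and a t reference on 17 df. Varying only the visit correlation and the stability of service effects moves it to about 83% to 86%. The unknown effect of baseline adjustment on the intracluster correlation widens the range to about 78% at the low end and above 90% at the high end, the latter only on values that the protocol does not give.

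**What to change.** Rewrite the sample size paragraph:

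- Replace the multiplied factors by the three-level form, (1 + 0.6)/2 + (12.75 − 1) × 0.062 = 1.5285 per patient.
- Use a t reference with (teams − 2) degrees of freedom.
- State that 221 analysed patients in 19 teams give about 83% power for the averaged effect under the stated assumptions.
- Say whether 0.6 and 0.062 are raw or baseline-adjusted, and show the power for both readings.
- If the 12-month contrast is made primary, quote its own figure, about 78% with t.

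The cost is one corrected paragraph and a less favourable power statement. The correction needs no extra patients. Keeping the 90% claim would: about 23 teams of 12 analysed patients, instead of 19.

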### Service and participant recruitment

Community intellectual disability services will be recruited across several regions in England which cover urban, semi-rural and rural areas.

We will ask two professionals from psychology, nursing, occupational therapy or speech and language therapy in each of the teams to volunteer to receive PBS training. A further one or two professionals who express interest will be on a waiting list in case of staff changes or drop outs. Each trained professional will have a maximum caseload of eight individuals at any time during the trial, i.e. a maximum of 16 service users per team. They may continue to provide generic input for other service users such as taking part in dysphagia assessments, assessment of capacity or day activities/home environment if practicable. However, as they will be delivering an intensive intervention, their generic workloads will need to be reduced. We anticipate that delivery of the intervention will be about 30% of their time. Once training has been completed, we anticipate that 12–14 service users across sites per month will be taken on for treatment.

